### Study design

EFFICHRONIC is a multicentre non-controlled prospective study with a duration of 3 years in five European settings: the Principality of Asturias in Spain, the area of Genoa in Italy, several regions in the UK, the Occitanic region in France and the area of Rotterdam in the Netherlands. The participating countries represent a wide range of social, economic and healthcare-related realities. The EFFICHRONIC intervention consists of the following phases: identification, recruitment and stratification of participants from vulnerable populations, implementation of the intervention and an economic and efficiency evaluation with a pre–post design. Additionally, guidelines and policy recommendations will be developed based on the project conclusions, this to allow the scaling-up of the intervention to other contexts.

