### Sample selection and recruitment

The potential participants are being identified by means of geographical, socioeconomic and clinical stratification processes. A distinction is made between the individual and social dimension of vulnerability, leading to different recruitment strategies that will be combined to be more efficient. First, geographical mapping of areas with a higher percentage of vulnerable population was done based on existing national and local indices in all participating countries. Consecutively, individualised recruitment will take place in these areas employing specifically designed actions. Multiple recruitment channels are used in coordination with local agents from the healthcare system, social services and community-based structures. More specifically, the following profiles and organisations are involved in recruitment: health professionals, pharmacists, social workers, non-governmental organisations, city councils and associations. The recruitment strategy at each study site is adapted to the specific local circumstances and collaborating organisations.

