### Stratification

To identify the people who will benefit most from the programme, individual socioeconomic and clinical parameters will be measured by a multidimensional stratification analysis. The tool used for this purpose, the ‘SELFY-MPI’, has been developed based on the validated Multidimensional Prognostic Index.^22^ The new tool is self-administrable and was specifically designed for EFFICHRONIC,^23^ adapting it to the broad adult population (not limited to the elderly) and incorporating the socioeconomic parameters from the Spanish Gijón scale: education, income, cohabitation, age and social support.^24^ Income categories are country-specific and built on the corresponding minimum wages.

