### Statistical analysis plan

Differences between baseline and follow-up measurements will be assessed employing the paired T-test (for normally distributed variables), the Mann-Whitney U test (for variables not normally distributed) and the Pearson χ^2^ test (for variable fractions). To adjust for multiple testing, one-way analyses of variance with post hoc testing (type Bonferroni) will be performed. The relationship of an outcome measure (T1) with explanatory variables will be determined using ordinary least squares regression analysis. The outcome measure (T0), (change in) other outcome measures, risk factors and social determinants may serve as explanatory variables. Additionally, the above-mentioned analyses will be repeated for each country separately and possibly for other subgroups (for variables which are likely to influence the effect of the intervention itself, eg, age and gender). All data from each of the five pilot sites will be anonymised and centralised at one study site for statistical analysis. Analyses will be performed with SPSS V.25.0.

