### Guidelines and policy recommendations

By the end of the project, guidelines and policy recommendations will be formulated based on the specific results of the participating countries. These recommendations will take into account acknowledged best practices at European level, to allow the scaling up of community-based interventions in vulnerable populations.

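### The pooled regression of the 6-month outcome does not name country among its explanatory variables, so determinant coefficients could partly reflect site differences

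*Protocol article*

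**What the plan says.** The Statistical analysis plan section of the protocol article describes the model: "The relationship of an outcome measure (T1) with explanatory variables will be determined using ordinary least squares regression analysis". It then names the candidate covariates: "The outcome measure (T0), (change in) other outcome measures, risk factors and social determinants may serve as explanatory variables". These are four classes of variable, and neither country nor site is among them.

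The same section continues: "Additionally, the above-mentioned analyses will be repeated for each country separately". It also says that "All data from each of the five pilot sites will be anonymised and centralised at one study site for statistical analysis". Read together, these sentences imply that the regression is first run on all five sites together and then within each country. Country appears as a way to split the data, but is not mentioned as a term in the pooled model.

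Three other sections bear on whether sites differ:

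- Study design: "The participating countries represent a wide range of social, economic and healthcare-related realities".
- Sample selection and recruitment: "The recruitment strategy at each study site is adapted to the specific local circumstances and collaborating organisations".
- Stratification: "Income categories are country-specific and built on the corresponding minimum wages".

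**The concern.** Sites that recruit through different partners, in different health and social systems, can be expected to differ in who takes part. The Study population section admits older people living alone or in nursing homes, people in financial difficulty, prisoners and isolated caregivers, and the article states no mix per site. Sites may also differ in mean 6-month outcome, even after adjustment for baseline, for reasons unrelated to any one participant characteristic.

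If both happen, a pooled regression without country credits part of the site difference to whichever determinant is commoner at the better or worse sites. At stake is the interpretation of the determinant coefficients, that is, which vulnerable participants do better at 6 months. The study has an interest in this, since its stratification tool is meant to find those who benefit most.

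**Working it through.** **The plan's own figure.** The plan gives no figure for this regression. Its only computed sample size, 978 analysed and 1223 included, reproduces: 977 by the normal approximation, 981 by the exact t calculation, and 978 / 0.8 = 1222.5, rounded up to 1223. The present point does not depend on it.

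**Bias formula.** Take a binary determinant with no true effect, equal site sizes (400 per country, from the Sample size section), and baseline unrelated to the determinant. Without country in the model:

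bias = covariance across sites of (prevalence, adjusted site mean) / total variance of the indicator.

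**Assumed inputs (not in the documents).** Prevalence 10, 20, 30, 40 and 50% at the five sites; baseline-adjusted site means 0, 0.1, 0.2, 0.3 and 0.4 SD, in the same order.

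- Covariance: (0.04 + 0.01 + 0 + 0.01 + 0.04) / 5 = 0.02.
- Total variance: 0.3 × 0.7 = 0.21.
- Bias: 0.02 / 0.21 = 0.095 SD.
- With half the spread in site means: 0.01 / 0.21 = 0.048 SD.

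**Dependence on alignment.** The 0.095 is the worst case for these values, because prevalence and mean are perfectly correlated across sites. Over all 120 orderings of the same site means, the bias runs from -0.095 to +0.095 and averages zero. The correlation of two randomly ordered sets of five has variance 1/(5 - 1), so the root-mean-square bias is 0.095 × 0.5 = 0.048 SD. With only five sites, a zero average over orderings does not guarantee a negligible bias in the ordering that occurs.

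**Against sampling error.** With an assumed residual SD of 1, the pooled standard error is 1/√(2000 × 0.21) = 0.049. A bias of 0.095 is 1.95 standard errors, so a true null would be declared significant at 5% about half the time. A bias of 0.048 gives about 16%.

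**Simulation.** Five sites of 400, 6-month outcome on baseline plus one continuous determinant with true effect 0. Country shares of variance are assumed. First, country effects on determinant and outcome perfectly aligned (400 replicates per row):

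| Country share, determinant | Country share, outcome residual | Coefficient without country | Rejection at 5% without country | Rejection with country |
|---|---|---|---|---|
| 0 | 5% | -0.001 | 5% | 5% |
| 2% | 1% | 0.011 | 10% | 6% |
| 5% | 2% | 0.029 | 29% | 5% |
| 10% | 2% | 0.037 | 47% | 4% |
| 20% | 5% | 0.087 | 100% | 6% |

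Over the whole grid the coefficient with country indicators was within 0.002 of zero, and rejection was 3 to 7%.

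Second, country effects drawn independently (1000 replicates per setting). Rejection without country was 4% when the determinant did not differ by country, and 8%, 12% and 22% for shares (5%, 2%), (10%, 2%) and (10%, 5%). With country it was 4 to 6% throughout.

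**What the per-country runs provide.** A regression within one country uses no between-country variation, so it is free of this bias. At n = 400 its standard error for a 30% determinant is 1/√(400 × 0.21) = 0.11 SD. One country's result is therefore a weak check on a pooled bias of 0.05 to 0.10 SD.

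**The case against.** The strongest reply is that the covariate sentence is permissive. It names candidates and excludes nothing, and a journal article may leave the final model to a fuller plan. This stands as far as it goes: the article does not say that country is left out. But it does choose to list covariate classes for a five-country model, and a pooled model without country would comply with that list.

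Second, the within-country regressions already give determinant estimates free of site differences, and a clash with the pooled coefficient would be visible. This also stands. They do not change the pooled coefficient, however, and the article does not say how a disagreement would be handled.

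Third, income categories tied to each national minimum wage partly harmonise income relative to local conditions. Agreed: that coding does not by itself create confounding. The case rests mainly on recruitment and setting.

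Stronger readings are tempting, and the documents do not support them:

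- A reader might infer that site differences will be reported as determinant effects. That requires both determinant and adjusted outcome to differ by country, which the documents do not establish.
- A reader might infer that the main conclusion is at risk. The Sample size section rests it on 10 tests (two SF-12 subscales in five countries), with paired t-tests as the basis of the calculation. No pooled determinant coefficient enters.
- A reader might infer that country results must be standardised to a common participant mix because "guidelines and policy recommendations will be formulated based on the specific results of the participating countries". That sentence does not say that countries will be ranked or compared on adjusted means. Case mix between countries is also a different question, which a country term would not answer.
- A reader might set 0.095 SD against the planning effect size of 0.185. The latter is a standardised pre-post change (4.3 / 23.2), while the former is a between-person difference in the 6-month outcome. The ratio has no clear meaning.

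**Conclusion.** The concern holds in a limited form. The pooled regression as listed does not secure adjustment for country, in a study whose own text describes heterogeneous countries and site-specific recruitment. Pooled determinant coefficients could therefore carry site differences.

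The size cannot be determined from the documents. It is nil if the determinant or the adjusted outcome does not differ by country, or if the two are uncorrelated across sites. It reaches about 0.095 SD under the assumed worst-case alignment, and half that with half the assumed spread in site means. The consequence is confined to the secondary determinant analyses. The change is worth making because it removes the risk at almost no cost.

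**What to change.** In the Statistical analysis plan section, state that country enters every pooled regression as a fixed effect (four indicators), so that determinants are estimated within country. State also that the per-country regressions serve as a consistency check, with the five coefficients for each determinant shown beside the pooled one.

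The cost is wording and four degrees of freedom out of about 2000 participants. Country must already be held with the centralised data, since per-country analyses are planned. The loss of precision is small. In the worked example the within-country variance of the indicator averages 0.21 - 0.02 = 0.19, so the standard error rises from 0.049 to 1/√(2000 × 0.19) = 0.051. No change to recruitment, data collection, sample size or the principal tests is needed.

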### Guidelines and policy recommendations

By the end of the project, guidelines and policy recommendations will be formulated based on the specific results of the participating countries. These recommendations will take into account acknowledged best practices at European level, to allow the scaling up of community-based interventions in vulnerable populations.

### Patient and public involvement

Patients were not involved in the design of the study, choice of outcome measures or definition of the recruitment strategies. However, some patients and caregivers take an active part in the conduct of the study as trained monitors, facilitating workshop sessions in the community. Study participants will be able to access the study results on request as stated in the participant information letter. News on the study progress is being published via various general and specialised media channels throughout the running of the study.

## Ethics and dissemination

It is not considered ethical to conduct descriptive research on vulnerable subjects without running specific interventions afterwards. For this reason, the study is not randomised-controlled, being consistent with the principle of social justice and the ethics of working with marginalised groups.^26^

The study follows the directives of the Helsinki declaration and the corresponding ethical regulations are being respected at each study site. In Occitanie, France, the Ethics Committee of the South-west and Oversees I in Toulouse (Comité de Protection des Personnes Sud-Ouest et Outre-Mer I) approved the study on 05 November 2018; study number 9788. In Genoa, Italy, the Regional Ethics Committee of Liguria (Il Comitato Etico della Regione Liguria) approved the study on 27 March 2018; study number 152–2018. In Rotterdam, the Netherlands, the Medical Ethics Review Committee (Medische Ethische Toetsings Commissie; METC) of the Erasmus MC University Medical Center—Rotterdam approved the study on 23 November 2017; study number MEC-2017–1116.

In Asturias, Spain, the Research Ethics Committee of the Principality of Asturias (Comité de Ética de la Investigación del Principado de Asturias) approved the study on 31 January 2017; study number 20/17. In the UK, the online decision tool and query line of the Health Research Authority were consulted and it was concluded that approval from the NHS Research Ethics Committee was not necessary.

Eligible participants will be informed of the objectives and the procedures of the CDSMP in person by the investigator and in writing by a participant information letter before enrolment. Only after a sufficient period of reflection and after clarification of all questions, the participant will be asked to sign two copies of the informed consent form. Participation in the study is completely voluntary and participants have the right to withdraw their consent from the study at any time for any reason.

Data processing, communication and transfer are done following the EU Regulation 2016/679 of the European Parliament and of the Council of 27 April 2016, also known as the General Data Protection Regulation.^27^ Only the research team that has to maintain confidentiality has access to all collected study data. Only impersonalised information may be transmitted to third parties. Information transmission to other countries will be carried out anonymously with a data protection level according to the mentioned regulation. The data will be collected and preserved in a codified way until the study is finished. The person responsible for data custody is responsible for the data file and treatment. At the end of the study, the data will be anonymised.

Via promotional materials, use of mass media, online activities, presentations at events and scientific publications, the project’s activities, progress and outcomes will be disseminated as described in a specific communication and dissemination plan. The strategy aims to enhance the engagement of healthcare and social care providers, civil society and public administration officers, all of which multipliers on account of their broad network and potential influence on the target population. Nevertheless, the main intended beneficiaries of the strategy are vulnerable people with long-term conditions and the health services serving these people. Accessing the hard-to-reach is one of the major challenges in EFFICHRONIC for which a solid strategy will be used.
